# Randomized controlled multicentre study comparing biological mesh closure of the pelvic floor with primary perineal wound closure after extralevator abdominoperineal resection for rectal cancer (BIOPEX-study)

**DOI:** 10.1186/1471-2482-14-58

**Published:** 2014-08-27

**Keywords:** Abdominoperineal resection, Rectal cancer, Radiotherapy, Primary perineal wound closure, Biological mesh, perineal wound infection, Perineal wound healing

## Abstract

**Background:**

Primary perineal wound closure after conventional abdominoperineal resection (cAPR) for rectal cancer has been the standard of care for many years. Since the introduction of neo-adjuvant radiotherapy and the extralevator APR (eAPR), oncological outcome has been improved, but at the cost of increased rates of perineal wound healing problems and perineal hernia. This has progressively increased the use of biological meshes, although not supported by sufficient evidence. The aim of this study is to determine the effectiveness of pelvic floor reconstruction using a biological mesh after standardized eAPR with neo-adjuvant (chemo)radiotherapy compared to primary perineal wound closure.

**Methods/Design:**

In this multicentre randomized controlled trial, patients with a clinical diagnosis of primary rectal cancer who are scheduled for eAPR after neo-adjuvant (chemo)radiotherapy will be considered eligible. Exclusion criteria are prior radiotherapy, sacral resection above S4/S5, allergy to pig products or polysorbate, collagen disorders, and severe systemic diseases affecting wound healing, except for diabetes. After informed consent, 104 patients will be randomized between standard care using primary wound closure of the perineum and the experimental arm consisting of suturing a biological mesh derived from porcine dermis in the pelvic floor defect, followed by perineal closure similar to the control arm. Patients will be followed for one year after the intervention and outcome assessors and patients will be blinded for the study treatment. The primary endpoint is the percentage of uncomplicated perineal wound healing, defined as a Southampton wound score of less than II on day 30. Secondary endpoints are hospital stay, incidence of perineal hernia, quality of life, and costs.

**Discussion:**

The BIOPEX-study is the first randomized controlled multicentre study to determine the additive value of using a biological mesh for perineal wound closure after eAPR with neo-adjuvant radiotherapy compared to primary perineal wound closure with regard to perineal wound healing and the occurrence of perineal hernia.

**Trail registration number:**

NCT01927497 (Clinicaltrial.gov).

## Background

Conventional abdominoperineal resection (cAPR) for distal rectal cancer is associated with relatively high rates of positive resection margins and iatrogenic tumour perforation. Pooled analysis of five European randomized controlled trials revealed that cAPR was an independent risk factor for local recurrence (19.7% versus 11.4%) and associated with a decreased 5-year survival rate (59% versus 70%) compared to low anterior resection
[1]. Following the total mesorectal excision (TME) plane all the way down to the pelvic floor, as performed in cAPR, results in the typical coning of the specimen and thereby compromising resection margins. Extralevator APR (eAPR) reduces the rate of positive resection margins and tumour perforation and improves oncological outcome based on a systematic review of non-randomized studies
[2]. The extralevator approach entails en bloc resection of the distal rectum, sphincter complex and levator muscles. Besides a change in surgical technique, neo-adjuvant radiotherapy has also contributed to better locoregional control in patients with distal rectal cancer.

Both wider excisions as a result of eAPR as well as increased use of neo-adjuvant (chemo)radiotherapy have significantly increased perineal wound healing problems, which have been reported in up to 59%
[3-6]. Furthermore, perineal hernia is more likely to occur with a reported incidence of up to 20%
[7]. Perineal wound complications may only consist of superficial infection or minor dehiscence, but are often more serious with major dehiscence or deep abscesses. Impaired perineal wound healing is a significant clinical problem being associated with increased hospital stay, the need for re-operation, and intensive wound care for several months. There is even a small proportion of patients in whom a presacral or perineal sinus remains. Quality of life may be severely impaired because of pain, smelly wound discharge, and interference with basic daily activities such as sitting and walking.

Internationally there is a trend towards the use of additional closure techniques after eAPR in an attempt to overcome this clinical problem. One of these techniques is the reconstruction of the pelvic floor with a biological mesh, but available literature data are scarce. A recently published review included 12 studies, of which six were only conference abstracts, with total numbers of included patients between 2 and 24
[8]. The percentage of minor wound complications in series with at least 5 patients ranged between 17% and 63%, and of major complications between 9% and 27%. Two larger studies not included in this review reported a perineal wound complication rate of 50% and 11% in 30 and 35 patients respectively
[9,10]. Autologous tissue flaps might also be an option and seems to be equally effective as a biological mesh
[11]. However, the routine use of flaps after eAPR for rectal cancer is controversial. The rectus abdominis muscle (RAM) flap cannot be combined with a laparoscopic approach, will add donor site morbidity, substantially increases operating time and often implicates assistance by a plastic surgeon
[12]. The gluteal flap does not disturb abdominal wall integrity, but seems not to prevent perineal hernia formation
[7].

The popularity of the use of biological meshes for eAPR is probably the result of its successful application in repair of complex and infected hernias of the abdominal wall as well as for example pelvic organ prolapses
[13,14]. However, the costs of a biological mesh ranges between 500 and 1800 euro per patient depending on the size of acellular porcine collagen implant and company. Based on the limited available data and costs of biological meshes, primary perineal wound closure after eAPR still remains the standard of care in many institutes. An unpublished survey among Dutch surgeons performed in 2012 revealed that 66% exclusively used primary perineal wound closure after APR, although the extralevator approach is not yet completely implemented at a national level. Using simple direct closure of the perineal wound after eAPR is supported by data from relatively large cohort series (104 to 282 patients), which reported perineal wound complication rates between 17% and 35%, with a proportion of patients who received radiotherapy between 31% and 60%
[5,15-17]. However, standardized perineal wound assessment was not used in any of these studies and complication rates may be underestimated because perineal wound healing was not a primary outcome parameter. This underlines the need for a randomized comparison of different perineal closure techniques after eAPR.

## Methods/Design

### Objective

The primary objective of this study is to determine the effectiveness of pelvic floor reconstruction using a biological mesh after eAPR with neo-adjuvant radiotherapy compared to primary perineal closure. It is hypothesized that biological mesh closure is superior to primary perineal closure in a cost-effective manner in terms of a higher primary perineal wound healing rate and a lower perineal hernia rate at reduced costs.

### Design

This is a multicentre, single blinded, randomized controlled trial, in which eligible patients will be randomized between pelvic floor reconstruction using a biological mesh (intervention arm) and primary closure of the perineal defect (standard arm) in a 1:1 ratio (Figure 
1). Randomisation will be performed pre-operatively by a central automated randomisation using the trial website, with stratification for age, sex and laparoscopic surgery. The allocation of treatment is blinded to the patient.

### Study population

Patients are eligible for this study when they meet the following inclusion criteria: age of 18 years or older, planned eAPR for primary rectal cancer, pre-operative (chemo)radiotherapy, life expectancy of more than 2 years, ability to return for all scheduled and required study visits, and written informed consent for study participation. Exclusion criteria are: previous pelvic irradiation for other cancers (i.e. prostate cancer), total pelvic exenteration or sacral resection above level S4/S5, sensitivity to porcine derived products or polysorbate, severe systemic diseases abibuffecting wound healing except diabetes (i.e. renal failure requiring dialysis, liver cirrhosis, and immune compromised status like HIV), collagen disorders (i.e. Marfan), enrolment in trials with overlapping primary endpoint or otherwise expected influence on wound healing (i.e. systemic therapy like anti-angiogenic agents). An interim review will be performed at 50 included patients (of the total of 104 patients). At 6 weeks after inclusion of these patients, the trial’s safety data will be evaluated. The steering committee will be supplied with the number of (serious) adverse events in both groups at this time point. If there is a skewed distribution of the number of (serious) adverse events between the two groups, an efficacy analysis can be performed at the discretion of the steering committee. Following these interim analyses, the steering committee will advise upon continuation of the trial.

### Intervention strategies

The perineal phase of the APR will be performed according to the principles of an extralevator approach, which means that the levator muscles will be laterally transected in order to leave a muscular cuff around the tumour. The coccyx will not be routinely resected, but only if indicated based on surgical exposure or oncological principles. The extent of excision of perineal skin and ischioanal fat will be as limited as oncologically justified. The eAPR specimens will be classified according to Phil Quirke and photographed in a standardized fashion. Patient positioning (prone or supine), the surgical approach for the abdominal phase (open or laparoscopic), and the use of an omental plasty are left to the discretion of the operating surgeon, because there is no conclusive evidence on which of these technical aspects is the most optimal with regard to perineal wound healing.

Closure of the perineum in the control arm consists of stitching the ischioanal and subcutaneous fat using interrupted Vicryl sutures in one or two layers. Subsequently, the skin will be closed using interrupted sutures according to the preference of the surgeon. Placement of a transabdominal or transperineal drain will be performed according to local protocols.

The intervention in the experimental arm consists of suturing an acellular biological mesh derived from porcine dermis in the pelvic floor defect (Strattice™, 6x10 cm). The mesh will be sutured at each side of the coccyx or distal sacrum with Prolene or Polydioxanone sutures (PDS). Laterally, the mesh is attached to the remaining of the levator complex and, anteriorly, to the transverse perineal muscle. A suction drain will be inserted and positioned on top of the mesh. The perineal subcutaneous fat and skin will be subsequently closed in layers similar to primary perineal closure as performed in the standard arm.

### Outcome parameters

Primary endpoint is the percentage of uncomplicated perineal wound healing defined as a Southampton wound score less than II at 30 days postoperatively.

Secondary endpoints of this study are the need for wound care, either in hospital or out of hospital and specified to frequency, duration, and type of wound dressing, the need for surgical re-intervention or re-admission for perineal wound problems, total hospital stay during one year of follow-up, incidence of asymptomatic and symptomatic perineal hernia, quality of life (EQ-5D-5 L, EORTC-30, EORTC-29RC, SF-36), and (in)direct medical and non-medical costs (clinical report forms, hospital information systems, modified health and labour questionnaire). In addition, perineal wound healing according to the Southampton wound grading will be repeated at 3, 6, 9 and 12 months postoperatively in order to determine differences in wound healing between the study arms over time. Differences in the incidence of persistent perineal or presacral sinuses, both clinically and by CT imaging, will be evaluated at 1 year of follow-up.

### Sample size calculation

The principal analysis will consist of an intention-to-treat comparison of the proportions of patients with primary uncomplicated perineal wound healing between both study arms. The hypothesis is to test superiority of the biological mesh assisted closure over primary closure of the perineum. The currently available literature is difficult to interpret with regard to perineal wound healing for the two interventions to be studied, hampering defining the expected difference in healing rate. Data on primary closure are mostly derived from cohort series in which patients were mostly operated upon before 2005
[3-7,10,19-23]. At that time, eAPR was only applied in a minority of centres. Furthermore, there has been an enormous increase in the use of neo-adjuvant radiotherapy in the past decade. These two developments in the treatment of distal rectal cancer have had a significant impact on perineal healing rate. In contrast, literature on biological mesh assisted perineal closure has been published recently only in patients undergoing eAPR and with high rates of neo-adjuvant radiotherapy
[7,9,10,20-23]. In addition, these studies had a specific focus on perineal wound healing, which results in more detailed data with a relative over-reporting of perineal wound complications compared to the historical data on primary closure in which perineal healing was most often a secondary endpoint that was retrospectively studied. Both the low percentage of eAPR in the primary closure group and relative over-reporting of perineal wound complications in the biological mesh led us to conclude that the available literature may underestimate the potential difference between both closure techniques.

Given the before mentioned lack of high quality data in the literature, we defined a clinically relevant difference in primary uncomplicated perineal healing which justifies the routine use of an expensive biological implant. This difference is considered to be 25%. A total number of 98 patients (49 per group) are needed to be able to detect a 25% increase in primary perineal wound healing by insertion of a biological mesh from 60% to 85%, applying a Chi2-test with a two-sided 0.05 significance level and with 80% power. With an estimated drop-out of 5%, a total number of 104 patients are required (52 per group).

### Data-analysis

The primary endpoint, the percentage of uncomplicated wound healing defined as a Southampton wound score of less than II at 30 days postoperatively, will be compared between the two study groups using a two-sided Chi-square test with a significance level of 0.05. The primary endpoint will be further explored by comparing wound scores as categorical variable using the Mann Whitney U test. Furthermore, differences in time to healing between the two groups will be analysed as a censored continuous variable using Kaplan-Meier survival analysis. Treatment effects will be expressed as a relative risk with 95% confidence interval. Any binary secondary outcome measures (e.g. hernia rate, re-operation rate, infection rates, etc.) will be analysed in the same way as the primary outcome. Quality of life data (e.g. EQ-5D-5 L, EORTC-30, EORTC-29RC, SF-36) will be graphically represented across all time points and analysed using a repeated measures analysis of variance. The scoring profiles from a patient on subsequent EQ-5D-5 L assessments up to month 12 will further be used to derive health utilities based on the most recent crosswalk value sets at the time of analysis
[24]. The health utilities will then be used to calculate quality adjusted life years (QALY) as the product sum of the utilities and the lengths of time preceding the repeated measurements.

The most recent Dutch guideline for costing in health care research will be applied to assign unit costs to observed health care resources in order to estimate the costs of care for each study group
[25]. Costs differences will be off-set against the difference in numbers of patients with uncomplicated perineal wound healing. Cost differences will also be off-set against the difference in quality adjusted life years to calculate the extra costs per QALY gained. Both economic analyses will be performed from a societal perspective, with a time horizon set at 12 months. In addition, the analyses will be repeated from a hospital care provider perspective to improve the study’s generalizability to countries with other health care systems. No discounting of effects and costs will be performed. Sensitivity analyses will be performed to account for sampling variability and key study parameters (unit costs of the closure procedure using the biological mesh, alternative utility weights of observed health states). Results will be displayed graphically with cost-effectiveness planes and acceptability curves.

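### The primary test and relative risk ignore the three randomisation strata, so if those factors predict healing the chi-square is mildly conservative and its interval somewhat too wide

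*Protocol article*

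**What the plan says.** The Design section describes central, pre-operative, 1:1 randomisation "with stratification for age, sex and laparoscopic surgery". It gives no age cut-off, block size or allocation method.

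Under Data-analysis, the primary endpoint (Southampton score below II at 30 days) "will be compared between the two study groups using a two-sided Chi-square test with a significance level of 0.05". On estimation the section says: "Treatment effects will be expressed as a relative risk with 95% confidence interval". Binary secondary outcomes follow the same approach as the primary. Neither the test nor the estimate refers to the stratification factors, and no adjusted analysis of the primary endpoint appears elsewhere in the article.

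The Sample size calculation section uses the same unadjusted test, "applying a Chi2-test with a two-sided 0.05 significance level and with 80% power", for healing of 60% against 85%. It concludes: "A total number of 98 patients (49 per group) are needed".

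**The concern.** Stratified randomisation balances the arms on the chosen factors. If a factor predicts the outcome, that balance reduces the true variance of the difference between arms. The plain chi-square and the usual interval for a relative risk still compute their standard error as if allocation had been unrestricted, so the variation between strata stays in. The test then rejects less often than its nominal 5% under the null, the interval is wider than it needs to be, and some power that the design could have delivered is not used.

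Choosing age, sex and laparoscopy for stratification suggests that they were thought worth balancing. An analysis that ignores them does not follow from that choice. The article names its primary test and effect measure, so this is a stated choice and not a detail left to a later document.

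**Working it through.** **Inputs from the article.** Healing 60% (control) and 85% (mesh); two-sided alpha 0.05; 80% power; 98 evaluable patients (49 per group); 5% drop-out; three stratification factors; 1:1 allocation.

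**Step 1: the plan's own figure.** For a chi-square test with pooled variance under the null and no continuity correction,

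n per group = [z₀.₉₇₅ √(2 p̄(1−p̄)) + z₀.₈₀ √(p₁(1−p₁) + p₂(1−p₂))]² / (p₂−p₁)²

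With p̄ = 0.725:
- 1.960 × √0.39875 = 1.238
- 0.842 × √0.3675 = 0.510
- (1.238 + 0.510)² / 0.25² = 48.9, rounded up to 49 per group

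Power at 49 per group is Φ[(0.25 × √49 − 1.238) / √0.3675] = Φ(0.845) = 80.1%. At 52 per group it is 82.4%. Drop-out: 98 / 0.95 = 103.2, rounded up to 104. The stated 98 and 104 are reproduced, and the planned power is reached without adjustment.

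**Step 2: what a stratified test would change.** The documents do not say how strongly the factors predict healing, so this is shown as a range. Assumed, and not in the documents: each factor has two levels at 50% prevalence, giving eight strata; permuted blocks of 4 within strata; the same odds ratio (OR) with healing for each factor. There were 40,000 simulated trials of 98 patients per setting. The tests compared are the plain chi-square and the Cochran-Mantel-Haenszel (CMH) test; the standard errors (SE) compared are those of the crude and the Mantel-Haenszel (MH) log relative risk.

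| OR per factor | Size, chi-square (60% v 60%) | Power, chi-square (60% v 85%) | Power, CMH | Change in power (points) | SE of log RR, crude / MH |
|---|---|---|---|---|---|
| 1 | 5.2% | 81.2% | 80.6% | −0.6 | 0.132 / 0.133 |
| 1.25 | 5.1% | 81.2% | 80.9% | −0.3 | 0.132 / 0.132 |
| 1.5 | 5.0% | 81.3% | 81.3% | 0 | 0.132 / 0.132 |
| 2 | 4.4% | 81.7% | 83.0% | +1.3 | 0.132 / 0.129 |
| 3 | 3.6% | 82.5% | 85.8% | +3.3 | 0.132 / 0.126 |
| 4 | 2.8% | 82.9% | 87.8% | +4.9 | 0.132 / 0.123 |

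The size of the CMH test stays between 4.9% and 5.2% throughout. On the log scale, the crude interval is about 2% too wide at OR 2 (0.1322/0.1294 = 1.02), 5% at OR 3 (0.1323/0.1257 = 1.05) and 8% at OR 4 (0.1322/0.1226 = 1.08). Below OR 1.5 the difference is negligible.

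Prevalences of 40%, 35% and 60% give the same pattern. A separate simulation under the main assumptions gave power, chi-square against CMH, of 80.8% v 80.3% at OR 1, 81.0% v 81.0% at OR 1.5, 81.4% v 82.7% at OR 2 and 82.3% v 85.5% at OR 3.

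**Step 3: a sparse secondary outcome.** The Discussion expects surgical reintervention to fall from 10% to 5%. With 49 per group that is 49 × 0.10 + 49 × 0.05 = 7.35, or about 7 events over eight strata. In 20,000 simulated trials per setting, fewer than five strata on average contributed information. Power, chi-square against CMH, was 14.8% v 13.8% at OR 1, 15.6% v 14.7% at OR 1.5 and 15.3% v 14.8% at OR 2. Here stratifying loses a little.

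**The case against.** The other side has a good case. An unadjusted chi-square is valid, pre-specified and the very test the trial was sized for, so design power and analysis agree. Any error is conservative, so a false claim of benefit is not at issue. The loss arises only if the factors are prognostic. The article gives no figure for this, and under Intervention strategies it says there is no conclusive evidence on which abdominal approach is best for perineal healing. The number of strata and the block size in the simulations are assumptions. A fuller protocol or analysis plan may add adjusted analyses.

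Most of this stands, and it limits the size of the point. It does not remove the mismatch, because the article itself fixes the primary test and effect measure without the factors.

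A reader might infer three stronger things that the documents do not support:
- **The trial is underpowered because of this choice.** It is not: power is 80.1% by formula and above 80% in every simulated setting.
- **Power is certainly lost and the interval is certainly too wide.** That depends on prognostic strength, which is not given. At an odds ratio of 1.5 or less per factor there is no material loss.
- **Stratifying can never do worse and should apply to every binary outcome.** It costs about half a point for the primary endpoint if the factors are not prognostic, and up to about one point for an outcome as rare as reintervention.

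**Conclusion.** The point holds in a conditional and modest form. Randomisation is stratified on three factors and the primary test and relative risk ignore them. If the factors predict healing, the test is conservative (size 4.4% at OR 2 and 3.6% at OR 3 per factor) and the interval about 2% to 5% too wide on the log scale. If they do not, the plain test is fine and very slightly the better of the two. What is forgone is possible extra precision. The stated 80% power is kept and type I error is not inflated.

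The direction follows from the design. The size rests on the assumed eight strata, blocks of 4 and equal odds ratios for the three factors. The trade still favours a stratified primary analysis: about half a point of power at risk, against gains of about 1 to 3 points at OR 2 to 3 and a test that holds its nominal level.

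**What to change.** Before outcome data are seen, amend Data-analysis as follows:

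- **Primary test:** a two-sided Cochran-Mantel-Haenszel test at 0.05, stratified by age group, sex and laparoscopic surgery.
- **Factor values:** those entered at randomisation. Randomisation is pre-operative, so the laparoscopy factor is the planned approach, whatever is done in theatre.
- **Effect estimate:** the Mantel-Haenszel relative risk with 95% confidence interval.
- **Sensitivity analysis:** the plain chi-square test with the unadjusted relative risk.
- **Binary secondary outcomes:** state the method for each, and do not carry the stratified test over automatically to rare events such as reintervention.

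The cost is wording. The factor values are already in the randomisation system, and the sample size of 104 stays as it is. The downside is up to about half a point of power for the primary endpoint if the factors prove not to be prognostic.
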